## Abstract

Spinal cord injury (SCI) patients require continuous rehabilitation post-discharge to ensure optimal recovery. This study investigates the effectiveness of home-based virtual reality fitness training (VRFT) as a convenient and accessible rehabilitation method for SCI patients. This randomized, double-blind, multicenter trial will enroll 120 participants, assigning them to either an 8-week VRFT program (exercise group) or a control group engaging in regular daily activities. The outcomes measured include muscle function, cardiopulmonary fitness, body composition, and physical performance. Our study will determine the safety and feasibility of VRFT in a home setting for SCI patients and evaluate whether these patients can effectively participate in such a program post-discharge. The results of this study are expected to inform future exercise protocols for SCI rehabilitation, offering valuable insights into the utility of VRFT as a therapeutic tool.

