### 2.9. Data Collection Methods and Analysis

Outcome measures will be collected before and after the 16 intervention sessions, excluding the sociodemographic and descriptive information.

The sample size determination was based on prior research findings [34]. A power analysis was conducted using G*Power software (version 3.1.2.) [39]. The analysis used an effect size of 0.5 for the outcomes, a power level of 80% (type II error of 0.2), and a significance level of 0.05. We calculated that 29 individuals per group would be required to achieve the necessary statistical power. Therefore, we plan to enroll 30 individuals per group, resulting in a total of 120 participants across the four groups. This calculation ensures sufficient power to detect meaningful differences between the intervention and control groups.

We will assess participant characteristics and baseline comparisons to assess the comparability between the exercise and control groups. A table will be provided to display the characteristics of individuals assigned by the group. Percentages and frequencies will be used to present categorical elements, and time intervals along with continuous elements will be summarized using medians, standard deviations, means, and interquartile ranges. This procedure secures the baseline equivalence between the groups.

An intention-to-treat framework will be employed for our statistical analysis. Kolmogorov–Smirnov analysis will be used to assess the normality of the dependent variables for the outcomes. The responsible variables will be characterized based on their distribution, utilizing either medians and interquartile ranges or means and standard deviations. To achieve the objective, hypothesis tests will be conducted for each outcome, positing that the exercise group will have superior outcomes compared to the control group. All estimates will be accompanied by intervals with 95% confidence level. Student’s *t*-test will be applied for independent samples that follow a normal distribution, while the Mann–Whitney U test will be utilized for data that do not conform to a normal distribution.

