We expect that VRFT will be deemed practical, given that the devices can be easily set up in participants’ residences and that individuals can efficiently master and advance with VRFT. Additionally, it is anticipated that individuals will find VRFT enjoyable and appreciate its advantages in their rehabilitation journey, avoiding negative outcomes like accidents or mishaps.

The results from this study will offer a framework for individuals with SCI to securely engage in VRFT and workout at home after hospital-based rehabilitation. Our plan is to present our results in academic publications and share them at symposia, distributing the information through meetings focused on SCI rehabilitation.

It is essential to recognize that this study will have limitations due to the small number of participants, with just 15 individuals assigned per exercise group. Undertaking a pilot study is a sensible initial step before investing substantial resources in the study; however, the limited sample size might restrict our capacity to identify meaningful variations among the groups. Following studies, our study plans to undertake an extensive study to assess the impact of VRFT conducted at home on physical outcomes, including muscle function, cardiopulmonary fitness, body composition, and functional abilities. The findings will guide future studies by providing insights into aspects such as physical measurements, sample size, VRFT duration, weekly frequency, exercise intensity, time, and type of interventions. Practical insights into home-based VRFT post-hospital discharge are essential for guiding future study endeavors. Our study focuses on how hospital-based professionals and fitness trainers can work together to facilitate the implementation of VRFT for individuals with SCI after their hospital discharge. We aim to make substantial progress in this area over the next few years. The increasing adoption of technology in home-based settings positions VRFT as a promising method to enhance rehabilitation intensity and improve health conditions for those recuperating for individuals with SCI.

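### Section 2.9 lets 'group' mean an arm in the power calculation and apparently a hospital in the total, so the size per arm is never stated and the power claim conflicts with the Discussion

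*Protocol article*

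**What the plan says.** The Abstract gives a total of 120 participants in two arms, "assigning them to either an 8-week VRFT program (exercise group) or a control group engaging in regular daily activities". Section 2.1 also describes exercise and control only, and names four hospitals. Section 2.3 randomizes 1:1 within each institution.

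Section 2.9 gives the sample-size inputs: "The analysis used an effect size of 0.5 for the outcomes", 80% power and "a significance level of 0.05". From these it obtains 29 per group. It continues: "Therefore, we plan to enroll 30 individuals per group, resulting in a total of 120 participants across the four groups". The next sentence asserts that power is sufficient for intervention versus control. The planned test is an independent-samples t-test, or Mann–Whitney U if the data are not normal. The hypothesis is worded directionally, "positing that the exercise group will have superior outcomes compared to the control group", but no one-sided test is declared.

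The Discussion gives another size, "with just 15 individuals assigned per exercise group", and adds that "the limited sample size might restrict our capacity to identify meaningful variations among the groups".

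**The concern.** The word 'group' does not keep one meaning. In the power calculation it is an arm, because the contrast named there is intervention versus control. In the total it must count something of which there are four, and the trial has two arms. In the Discussion it is something with 15 people in it. A reader who takes the arm meaning through to the total gets 60 participants, not 120.

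What is at stake is the power claim. It is attached to a per-group number, and a reader cannot tell from the text which number of participants per arm is being called sufficient. The two places that comment on adequacy also point in opposite directions: 2.9 gives an assurance and the Discussion a caution.

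**Working it through.** **Inputs.** Effect size 0.5, power 0.80, alpha 0.05, 29 rounded to 30 per group, and total 120 (all Section 2.9); two arms (Abstract, 2.1); four hospitals (2.1); 1:1 within hospital (2.3); 15 per exercise group (Discussion). Two assumptions are mine, because the article does not say: the effect size is Cohen's d, and sidedness is open, so both are shown. No dropout is assumed.

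**Step 1: which meaning of 'group' fits the numbers.**
- Group = arm: 2 x 30 = 60. This does not give 120.
- Group = hospital: 4 x 30 = 120. Split 1:1, each hospital has 30 / 2 = 15 per arm, and each arm has 4 x 15 = 60.

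The second reading accounts for 30, 120 and 15, and agrees with the Abstract's total in two arms.

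**Step 2: the plan's own 29.** For a two-sample comparison of means, n per arm = 2(z_alpha + z_power)² / d².
- Two-sided: 2(1.960 + 0.842)² / 0.25 = 62.8, so 63. The t-test solution is 63.77, so 64.
- One-sided: 2(1.645 + 0.842)² / 0.25 = 49.5, so 50. The t-test solution is 50.15, so 51.
- Mann–Whitney (dividing by a relative efficiency of 0.955): about 67 two-sided, 53 one-sided.

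The figure of 29 is not reproduced. Values close to it arise only from procedures other than the planned comparison: a one-sided paired t-test (27), a one-sided signed-rank test (28) or a test of a correlation of 0.5 (about 29).

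**Step 3: power at each candidate size.** Noncentral t, d = 0.5, alpha 0.05, noncentrality 0.5 x √(n/2), degrees of freedom 2n − 2.

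| n per arm | noncentrality | power, two-sided | power, one-sided |
|---|---|---|---|
| 15 | 1.37 | 26% | 38% |
| 29 | 1.90 | 46.5% | 59% |
| 30 | 1.94 | 48% | 61% |
| 60 | 2.74 | 77.5% | 86% |

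Only the last row corresponds to the design as described. At 60 per arm the effect detectable with 80% power is 0.52 SD two-sided or 0.46 SD one-sided. The other rows show that neither 29 nor 30 per arm reaches 80% under either sidedness.

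**The case against.** The strongest reply is that nothing is numerically broken. Once 'group' is read as hospital, 30, 120 and 15 all agree, and 4 x 30 = 120 is correct. That stands. A reader might infer three irreconcilable sample sizes, or a plan for two arms of 30; the documents support neither, and no sentence states 30 per arm.

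A reader might also infer that the unit of comparison is left open, or that each hospital will be tested separately with 15 against 15. The text does not support this. Section 2.9 names exercise versus control in the power statement, the baseline comparison and the hypothesis, and no hospital-level test is planned. The 26% power at 15 per arm therefore belongs to a test nobody proposes.

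The Discussion should not be overread either. It says the size might limit detection, in a self-described pilot, and does not say that the trial is too small. Finally, Figure 1 is not shown and may display the allocation per site, so taking the four groups to be hospitals is a strong inference rather than a stated fact.

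Reconciling the totals does not rescue Section 2.9. On the hospital reading, a two-arm requirement has been applied to sites while the power sentence still speaks of arms, and the calculation behind it is not reproducible. The difference in tone between 2.9 and the Discussion is milder than a flat contradiction, but both cannot stand as written.

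**Conclusion.** The point holds as a defect in how the sample size is defined and justified. The design the numbers describe is 60 per arm, a figure the article never gives. Its power at an effect size of 0.5 is about 77.5% two-sided or 86% one-sided, so whether the 80% target is met depends on a sidedness the text does not fix. The stated basis of 29 per group falls well short of what the inputs require (64 or 51 per arm). The result rests on Cohen's d, the t-test, no dropout and the hospital reading of the four groups. It is worth correcting because the trial relies on these statements and restating them is cheap. It does not show that the trial is badly underpowered.

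**What to change.** - **Section 2.9, size:** state two arms, 60 per arm, 120 in total, recruited at four hospitals with about 15 per arm at each, and name the pooled exercise-versus-control comparison as the one that is powered.
- **Section 2.9, power:** replace the 29-per-group basis with the power that 60 per arm provides. Say that 0.5 is Cohen's d, if that is what was meant, and state whether the test is one- or two-sided: about 77.5% two-sided or 86% one-sided. If 80% two-sided is to be kept, 64 per arm (128 in total, 8 more than planned) is needed. One-sided, 51 per arm (102 in total) suffices, and 120 already exceeds it.
- **Discussion:** replace the figure of 15 with 60 per arm (15 per arm per hospital), and reword the limitation so that it agrees with the restated power.

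The cost is a rerun of the calculation and a few sentences. Relabelling the groups alone would not be enough, because it would leave the unsupported 29 in place. The recruitment target of 120 changes only if the sponsor insists on 80% two-sided.

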### 2.3. Randomization

Following the acquisition of informed consent from the participants, each team supervisor will identify and refer suitable candidates for the study. Subsequently, an independent statistician, not affiliated with the study team, will conduct the randomization process. Within each institution, participants will be categorized into two distinct subgroups through a block randomization approach. By employing blocks of size two in each stratum, an equal distribution ratio of 1:1 between the experimental and control groups will be achieved.

The randomization schedule will be generated utilizing SPSS software version 23.0 (IBM Corp., Armonk, NY, USA). The statistician responsible for the randomization will determine the block size and seed number through a random selection process. Thereafter, the randomized allocations will be sealed in packets, each designated for a participant, and delivered to the manager when the trial begins.

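### The planned t-test or Mann-Whitney U uses neither the baseline values nor the stratifying hospital, and does not say whether follow-up or change is tested; one prespecified ANCOVA would be more efficient at no data cost

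*Protocol article*

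**What the plan says.** Section 2.9 sets out the whole comparison. Kolmogorov-Smirnov "analysis will be used to assess the normality of the dependent variables for the outcomes". Student's t-test "will be applied for independent samples that follow a normal distribution", and Mann-Whitney U takes over where normality is not met. No regression model, covariate, change score or hospital term appears anywhere in the article, and the variable to be tested (follow-up value or change) is not named.

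Two other parts of the design bear on this:

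- Outcomes are assessed before randomisation (section 2.5) and again after the 16 sessions (section 2.9), so a baseline value of each outcome is planned for every participant.
- Section 2.3 makes the hospital a stratification factor: "Within each institution, participants will be categorized into two distinct subgroups through a block randomization approach". Blocks are of size two and the ratio is 1:1.

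The only stated use of the baseline data is a comparability table, of which section 2.9 says: "This procedure secures the baseline equivalence between the groups".

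**The concern.** The analysis does not follow the design. Three things are at stake.

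1. **Baseline.** An independent-samples test on follow-up values leaves stable differences between participants in the error term. A test on change scores uses baseline, but with a fixed slope of one, which adds noise when the correlation between the two measurements is modest. ANCOVA estimates the slope. Since the article does not say which variable is tested, the size of the loss cannot be pinned down, and the ambiguity is itself a defect.
2. **Hospital.** Balancing allocation within hospital removes hospital differences from the true variance of the treatment contrast. A two-sample test still counts them in its estimated variance, so its standard error is too large.
3. **Normality pretest.** The data decide whether an outcome is analysed as a mean difference or a rank comparison. Across many outcomes, the effect measure may differ from one to the next for reasons fixed only after the data are seen.

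A baseline table can describe the groups but cannot secure their equivalence. Chance imbalance in a prognostic baseline value is handled by adjustment.

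**Working it through.** **Inputs from the article.** Section 2.9: "The analysis used an effect size of 0.5 for the outcomes, a power level of 80% (type II error of 0.2), and a significance level", which is set at 0.05. Sidedness is not stated; two-sided is used here and one-sided is taken up under the objection. Total enrolment is 120, which at 1:1 is 60 per arm. The Discussion's 15 per exercise group, over four hospitals, also gives 4 × 15 = 60.

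**Inputs assumed.** The baseline to follow-up correlation ρ (0.3 to 0.8) and the hospital intraclass correlation (ICC, 0.1 or 0.2). The article gives neither.

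**The plan's own figure.** The stated 29 per group does not reproduce. For a two-sided two-sample t-test at d = 0.5, the noncentrality is d·√(n/2). With n = 29 this is 0.5 × √14.5 = 1.904, giving 46% power; 80% needs 64 per arm. That is a separate matter, so the comparison below uses 60 per arm.

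**Formulas.** With d in post-test SD units and n = 60 per arm:

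- Follow-up t-test: variance factor 1, df = 118.
- Change-score t-test: variance factor 2(1 − ρ), df = 118.
- ANCOVA on arm, baseline and four hospitals: variance factor 1 − ρ², df = 120 − 6 = 114.
- Noncentrality = 0.5/√(factor) × √30; power from the noncentral t.

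Follow-up test: 0.5 × 5.477 = 2.739, power 77.5%. ANCOVA at ρ = 0.5: 0.5/√0.75 = 0.577; 0.577 × 5.477 = 3.162; power 88.0%.

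| ρ | Change factor | Change power | ANCOVA factor | ANCOVA power | Gain over follow-up (77.5%) | Gain over change |
|---|---|---|---|---|---|---|
| 0.3 | 1.40 | 63.1% | 0.91 | 81.2% | 3.7 | 18.1 |
| 0.5 | 1.00 | 77.5% | 0.75 | 88.0% | 10.5 | 10.5 |
| 0.6 | 0.80 | 85.9% | 0.64 | 92.4% | 14.9 | 6.5 |
| 0.7 | 0.60 | 93.9% | 0.51 | 96.7% | 19.2 | 2.8 |
| 0.8 | 0.40 | 99.0% | 0.36 | 99.5% | 22.0 | 0.5 |

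Gains are in percentage points. ANCOVA is ahead of both readings at every value shown.

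**Hospital term.** Take four hospitals with 15 per arm, total variance 1 and ICC 0.1. The variance relevant to the contrast is 0.9. The two-sample test expects to estimate 0.9 + 0.1 × 90/118 = 0.976, where 90 = 2 arms × 15 × 3 hospital degrees of freedom. Its standard error is too large by √(0.976/0.9) = 1.041. By simulation, its type I error is about 4.3% at ICC 0.1 and 3.6% at ICC 0.2. Adding hospital alone raises power from about 79.4% to 81.7% at ICC 0.1.

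**Pretest.** In simulations of the Kolmogorov-Smirnov rule with normal data (2,500 runs per scenario, ICC 0 to 0.1), type I error ran from 3.8% to 5.2%. In one log-normal scenario it was 5.0%. The rule almost never rejected normality in normal samples, and did so in 89% to 99% of the log-normal samples.

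**The case against.** The strongest reply is that the stated tests are valid under randomisation, and that several more severe readings go beyond the text.

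- **That baseline is ignored outright.** A reader might infer this, but the article never says that the follow-up value alone is tested. If change scores are meant, the gain at ρ = 0.7 falls from about 19 points to about 3. At ρ = 0.5 or below, change scores bring no benefit over follow-up values and the case for ANCOVA is undiminished.
- **That most of the precision is wasted.** Against a follow-up test, the variance cut is 25% to 49% at ρ = 0.5 to 0.7 and only 9% at 0.3. The article gives no correlation or variance split for any outcome.
- **That the trial misses its stated power.** The 77.5% assumes a two-sided test. The hypothesis is directional, "positing that the exercise group will have superior outcomes compared to the control group", and sidedness is not given. One-sided, the follow-up test has 86%. ANCOVA is still higher (89% at ρ = 0.3, 93% at 0.5).
- **That the pretest inflates false positives.** It did not in the simulations.
- **That Mann-Whitney contradicts the promised 95% intervals.** An interval can be attached to it, and which one is detail that an analysis plan may hold.

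It also stands that raw-scale ANCOVA is not always best: in the log-normal scenario at ρ = 0.7, Mann-Whitney had 99% power against 94%. This is a reason to prespecify the scale, and does not rescue the pretest rule.

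**Conclusion.** The point holds as an efficiency and prespecification recommendation. The article itself states the analysis, so this is a choice made poorly and not a detail left to another document.

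The gain from ANCOVA is about 4 to 22 percentage points over a follow-up test, and about 18 falling to under 1 over a change-score test. This rests on 60 per arm, d = 0.5 in post-test SD, two-sided 0.05, and assumed correlations of 0.3 to 0.8. The direction is secure over that range; the size is not known.

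Nearly all of the gain comes from baseline. The hospital term adds only about 2 points at ICC 0.1, and its case is that omitting a stratification factor makes the test conservative. The fault of the pretest is that the effect measure depends on the data and may differ between outcomes. The sentence on baseline equivalence is a wrong claim about a descriptive table, with no shown effect on inference.

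**What to change.** In section 2.9, replace the pretest rule with one prespecified linear model for each continuous outcome: post-intervention value on arm, baseline value of the same outcome, and hospital. Report the adjusted mean difference with its 95% confidence interval.

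- Fix the scale or transformation of each outcome before unblinding.
- Use a rank-based ANCOVA as a sensitivity analysis.
- Keep the baseline table as description and delete the statement that it secures equivalence.
- State the sidedness of the tests.

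The cost is analysis wording only: no new data, visits or participants. The fitted models would also supply the baseline correlations and adjusted variances needed to size the larger study foreseen in the Discussion.

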### 2.4. Random Assignment

The research implements a double-blind methodology ensuring that neither the individuals involved nor the assessors know the allocation of the groups. To maintain blinding, independent assessors who are unaware of the group assignments will conduct all evaluations. Additionally, participants will be instructed not to discuss their specific activities with the assessors or other participants. Trainers administering the interventions will be kept unaware of the study details to minimize possible prejudice to the integrity of outcomes, thus strengthening the research results’ validity. Nonetheless, it should be noted that the principal investigator conducting the study will be aware of the group assignments due to the nature of the trial. Participants in the control group will adhere to their usual daily routines without any additional exercise intervention. They will continue with their regular activities of daily living (ADLs) as they did before the study, without any structured or guided exercise program.

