### 2.6. Program

The training program consists of 1 h classes conducted biweekly over a period of 2 months, as detailed in Table 1. Participants in the exercise group will have access to the VRFT devices not only during the biweekly classes but also at home throughout the trial period. This will allow the participants to engage in additional sessions as desired.

The rehabilitation protocol for spinal cord injury comprised cardiovascular and strength training exercises, as well as practical exercises focusing on the extremities and core. Furthermore, specialized programs were designed considering the goals and the type of exercise, time, frequency, duration, and intensity, adhering to the guidelines of the American College of Sports Medicine. The intervention program will incorporate the use of the Ringfit Adventure (RA) game for the Nintendo Switch (NS). (Figure 2). RA, a fitness program for the Nintendo, utilizes semi-immersive technology.

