Individuals with SCI will require an NS system, a Ring-Con (RC) (a flexible exercise ring held by the participant), a Bluetooth operator (attached to the RC and the other fastened to a leg strap on the participant’s quadriceps), and a monitor for this training class. The class is scheduled twice a week over eight weeks. Each class will be 1 h long, consisting of 10 min for warming up, 10 min for cooling down, and 40 min dedicated to the primary exercise session. RA is an action role-playing fitness game that advances the storyline through the player’s physical activities, which directly influence the character’s on-screen movements. These exercises are performed with the aid of the RC and thigh band [30]. The RC contains highly accurate pressure and tension detectors that capture and translate the individual’s movements [31]. Additionally, the Bluetooth operator features an infrared motion sensor capable of tracking the participant’s pulse rate [32]. RA has the capability to assess the ideal intensity of physical activities tailored to each individual and modify it according to biological signals either lowering or raising the activity level. In the first class, the virtual coach determines the intensity of physical activities and then progressively modifies them according to feedback from later sessions. The research staff will consistently supervise individuals in the exercise group, who will encourage participants to sustain the 16-session class at 60% to 80% of the individual’s baseline and the highest heart rate. Participants will be guided to keep their exertion within the range of 4 to 8 on the modified Borg CR10 rating of perceived exertion scale, which translates to a perception of effort from ‘moderate’ to ‘vigorous’ [33]. Participants in the comparison group will adhere to their normal routines and will not receive any specific intervention throughout the study.

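### If trainers or classes in the exercise arm are shared, as the article suggests but does not state, the planned independent-samples test can give intervals that are too narrow

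*Protocol article*

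**What the plan says.** **Analysis.** Section 2.9 tests every outcome for superiority of exercise over control and attaches 95% intervals. Student's t-test "will be applied for independent samples that follow a normal distribution"; the Mann–Whitney test replaces it otherwise. No term for centre, trainer or class is named. Section 2.3 randomises individuals 1:1 within each institution in blocks of two, so centre is a randomisation stratum.

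**Delivery to the exercise arm.**
- Section 2.4 refers to "Trainers administering the interventions".
- Section 2.6 gives exercise participants the devices "not only during the biweekly classes but also at home throughout the trial period", which sets classes apart from home use.
- Section 2.6 also states: "The research staff will consistently supervise individuals in the exercise group".
- The Discussion (section 3) says that training takes place wholly in the home.

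**Controls** keep their usual routine, with no class, trainer or supervision (sections 2.4 and 2.6).

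**Numbers.** Section 2.9 plans 120 participants. Section 3 describes the study as small, "with just 15 individuals assigned per exercise group".

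**The concern.** Where one trainer, class or supervisor serves several exercise participants, differences between deliverers in coaching, encouragement or adherence make those participants' outcomes alike. Nothing comparable acts on controls. The design is then partially nested: clustered in one arm and independent in the other. The t-test and the Mann–Whitney test both treat all observations within an arm as independent, so they would understate the variance of the exercise mean.

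At stake are the coverage of the 95% intervals, the 5% level of the superiority tests, and the reading of the result. A difference driven by one good trainer could be taken for an effect of the training in general. The article says that the results should guide the sample size of a later, larger study. That study would need an ICC, which cannot be estimated unless deliverers are recorded.

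**Working it through.** **The plan's own figure.** The only related figure is the sample size in section 2.9: effect size 0.5, 80% power, level 0.05, 29 per group. For two independent means, two-sided, n = 2(1.96 + 0.84)²/0.5² ≈ 63 per arm (64 with the t distribution), or 50 to 51 one-sided. The figure of 29 is not reproduced. That is a separate matter and does not bear on clustering. The plan has no figure for clustering to reproduce.

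**Inputs from the article.** 120 participants at 1:1 give 60 per arm. Four centres give 60/4 = 15 exercise participants each.

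**Assumed inputs.** Cluster size m and intraclass correlation ρ are not in the article. I take m = 15, 5 or 3, ρ = 0.01 to 0.10, total variance 1 in each arm, and clustering in the exercise arm only.

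**Formulas.**
- Design effect in the exercise arm: D = 1 + (m − 1)ρ.
- True variance of the arm difference: (D + 1)/60. The t-test uses about 2/60, a standard error of 0.183.
- Variance ratio: R = (D + 1)/2.
- True two-sided type I error: about 2[1 − Φ(1.96/√R)]. Coverage is one minus this.

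| m | ρ | D | R | true SE | type I, formula | type I, simulated |
|---|---|---|---|---|---|---|
| 15 | 0.01 | 1.14 | 1.07 | 0.189 | 5.8% | 5.6–5.8% |
| 15 | 0.02 | 1.28 | 1.14 | 0.195 | 6.6% | 6.6% |
| 15 | 0.05 | 1.70 | 1.35 | 0.212 | 9.2% | 9.0–9.2% |
| 15 | 0.10 | 2.40 | 1.70 | 0.238 | 13.3% | 13.2–13.5% |
| 5 | 0.01 | 1.04 | 1.02 | 0.184 | 5.2% | 5.2% |
| 5 | 0.05 | 1.20 | 1.10 | 0.191 | 6.2% | 6.4% |
| 5 | 0.10 | 1.40 | 1.20 | 0.200 | 7.4% | 7.4–7.5% |
| 3 | 0.01 | 1.02 | 1.01 | 0.183 | 5.1% | 4.9–5.0% |
| 3 | 0.05 | 1.10 | 1.05 | 0.187 | 5.6% | 5.6% |
| 3 | 0.10 | 1.20 | 1.10 | 0.191 | 6.2% | 6.0% |

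Simulations used 40,000 trials per setting. At m = 15, coverage of the nominal 95% interval falls from about 94% (ρ = 0.01) to about 87% (ρ = 0.10). With m = 1 or ρ = 0, D = 1 and there is no inflation.

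**Centre differences common to both arms.** Let these have variance share c. Arms are balanced within centre, so they cancel from the difference, whose true variance is 2(1 − c)/60. They stay in the variance that the t-test uses. The between-centre sum of squares in an arm is 15 × 3 × c on 59 degrees of freedom, so that variance is about 2(1 − c + 45c/59)/60. At c = 0.05 the true SE is 0.178 against 0.181 used, and type I error is about 4.6%. At c = 0.10 they are 0.173 and 0.180, and it is about 4.1%.

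**Both together (simulated).** At m = 15 and ρ = 0.05, type I error is 9.0%, 8.8% and 8.5% for c = 0, 0.05 and 0.10. At ρ = 0.10 it is 13.3%, 12.9% and 12.6%. At m = 5 and c = 0.05 it is 4.8%, 5.0%, 5.8% and 7.0% for ρ = 0.01, 0.02, 0.05 and 0.10.

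**Centre as a fixed effect alone** does not remove the inflation: 9.2–9.9% at ρ = 0.05 and 13.7–14.6% at ρ = 0.10 (m = 15). A trainer effect acts in one arm, so it appears as a centre-by-arm difference, which a centre main effect cannot absorb.

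**The case against.** The strongest objection is that shared delivery is not documented. Section 2.6 uses the word class for a one-hour session, and no section gives a group format, class size, number of trainers or caseload. Several statements point to individual delivery: training wholly at home (section 3), a console and monitor for the participant, and intensity set by the software for each person. This stands. Sharing is an inference, though a fair one. Sixty participants with 16 one-hour sessions each make 960 participant-hours, and nothing suggests a separate trainer or supervisor for each person. Individual tailoring by the game does not remove differences in coaching or supervision.

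A reader might take "with just 15 individuals assigned per exercise group" as proof of clusters of 15. The documents do not support that. It sits in a remark on small sample size and fits the number of exercise participants per centre. It does not show that one trainer or class serves all 15. The largest figures above depend on that assumption.

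A reader might also infer that having four centres in itself inflates false positives. It does not: differences common to both arms act the other way, and with caseloads of 3 to 5 they can cancel much or all of the inflation. With caseloads of 15 and ρ of 0.05 or more they offset little.

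Finally, an article may leave delivery logs and sensitivity analyses to the full protocol or analysis plan. Their absence is therefore no fault. What remains is that the article fixes an independence-based test beside a description that suggests clustering in one arm, and contradicts itself on the setting.

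**Conclusion.** The point holds conditionally. The article fixes a two-sample test that assumes independence and omits the centre stratum, while describing trainers, classes and supervision in one arm only. If delivery is shared, intervals may be too narrow and tests too liberal. Type I error is about 6% to 13% with an assumed caseload of 15 and ICC of 0.01 to 0.10, about 5% to 7% with caseloads of 3 to 5, and 5% with no sharing or ICC 0. The problem is material only with large caseloads and an ICC of about 0.05 or more, and neither is documented. The documents do not support the unconditional statement that shared classes or trainers invalidate the planned analysis. Confidence is medium because the ICC and caseload are assumptions.

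**What to change.** 1. Reconcile sections 2.6 and 3 on where and how sessions take place, and state class format, number of trainers and caseload.
2. Record the trainer or class for each exercise participant during delivery, when it is easy to capture.
3. Keep the main between-arm comparison and include centre, the randomisation stratum, in its model.
4. Beside it, pre-specify a partially nested sensitivity analysis: a mixed model with a random trainer or class effect in the exercise arm only, centre as a fixed effect, and Satterthwaite or Kenward–Roger degrees of freedom.
5. Report the arm difference by centre. If there is one trainer or class per centre, state that the main interval is conditional on those four.

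**Cost.** One identifier and one extra model, with no added patients or procedures. The downside is a wider and imprecise sensitivity interval when clusters are few. With four clusters of 15, a test based on exercise cluster means, without centre, has a half-width of about 0.40 to 0.48 SD at ICC 0 to 0.05, against 0.36 SD for the t-test. With centre also fixed and one trainer per centre, the trainer variance rests on 4 − 1 = 3 degrees of freedom. The half-width could then reach about 3.18 × 0.183 = 0.58 SD at ICC 0 and 3.18 × 0.212 = 0.67 SD at ICC 0.05. For this reason it belongs beside the main comparison and should not replace it.
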